**List of abbreviations**

|         |                                                                         |
|---------|-------------------------------------------------------------------------|
| AE      | Adverse Event                                                           |
| ADR     | Adverse Drug Reaction                                                   |
| BMI     | Body Mass Index                                                         |
| AIS-5   | Athens Insomnia Scale                                                   |
| CSSRS-S | Columbia Suicide Severity Rating Scale - Screener                       |
| GAD-7   | General Anxiety Disorder 7 Item Scale                                   |
| HREC    | Human Research Ethics Committee                                         |
| eCRF    | Electronic Case Report Form                                             |
| EQ-5D   | EuroQol 5D                                                              |
| HRBS    | HIV Risk Behaviour Scale                                                |
| HSU     | Health Service Utilisation                                              |
| ITT     | Intention-To-Treat                                                      |
| MedDRA  | Medical Dictionary for Regulatory Activities                            |
| PGI     | Patient Global Impression                                               |
| PHQ-9   | Patient Health Questionnaire – 9                                        |
| RCT     | Randomised Controlled Trial                                             |
| SAE     | Serious Adverse Event                                                   |
| SOC     | System Organ Class                                                      |
| TLFB    | Timeline Followback                                                     |
| TSQM    | Treatment Satisfaction Questionnaire for Medication Version 2           |
| WPAI-GH | Work Productivity and Activity Impairment Questionnaire: General Health |

## 1. Administrative information

**Project title:** Tina Trial: A phase 3 randomised double-blind placebo-controlled trial of mirtazapine as a pharmacotherapy for methamphetamine dependence

**Protocol Version Number:** Version 12.0, 28th October 2024

**Registration:** Australian and New Zealand Clinical Trials Registry (ACTRN12622000235707).  
Registered on February 9, 2022. The Universal Trial Number (UTN): U1111-1271-8220.

**Overall study sponsor:** University of New South Wales. This research is being conducted jointly by the NHMRC investigator team and their institutions under a co-sponsorship arrangement. Please refer to the study protocol for details.

**Funding body:** Medical Research Future Fund (Grant No. 2007155)

## 1.1 Version history

| Version | Date      | Description of Change              | Brief Rationale                                                                           |
|---------|-----------|------------------------------------|-------------------------------------------------------------------------------------------|
| 1.0     | 23/4/2025 | N/A                                | N/A                                                                                       |
| 2.0     | 1/5/2025  | Correction to scoring of the AIS-5 | The scoring of the AIS-5 was incorrect and the score range cited as 0-20 instead of 0-15. |
|         |           |                                    |                                                                                           |
|         |           |                                    |                                                                                           |

## 2 Introduction

### 2.1 Rationale

Methamphetamine (also known as “crystal meth” or “ice”) is a significant and growing global public health concern with an estimated 7.4 million people worldwide dependent on the drug [1, 2] (i.e., experiencing what is now termed a ‘methamphetamine use disorder’ under the DSM 5).

Methamphetamine use disorder is a chronic, relapsing condition [3] that is associated with elevated mortality, increased incidence of HIV and hepatitis C infection, poor mental health (suicidality, psychosis, depression, and violence), and increased risk of cardiovascular events [4]. Use accounts for a significant excess number of psychiatric hospital admissions and emergency department presentations in Australia [5]. In the USA, methamphetamine is increasingly used in conjunction with opioids, and this is contributing to the growing number of opioid-related overdose deaths [6].

Currently there are no approved pharmacotherapies to assist with the treatment of methamphetamine use disorder [7, 8]. Although individual trials have found positive results (e.g., long-acting slow-release amphetamine preparations [9] and combination naloxone and bupropion [10]), many promising options have failed to produce the expected reductions in methamphetamine use [11, 12], and there remains insufficient evidence to support any pharmacotherapy option for methamphetamine use disorder [13]. Effective pharmacotherapy has the potential to dramatically increase treatment coverage, enhance treatment engagement and retention, and mitigate against poor health outcomes for people with methamphetamine use disorder.

One promising pharmacotherapy candidate is the generic tetracyclic antidepressant, mirtazapine, with significant reductions in methamphetamine use found in two preliminary phase 2 trials in the United States [14] [15]. The first trial (N = 60) found 12 weeks of mirtazapine (30 mg/day) significantly reduced methamphetamine use relative to placebo amongst sexually active men who have sex with men [14]. The second trial replicated these positive results after 24-weeks of mirtazapine treatment with a larger sample of cisgender men, transgender men, and transgender women, who have sex with men (N = 120) (positive urine test results at 24 weeks relative to placebo 63% vs. 74%; RR 0.75, 95% CI 0.56 – 1.00, p = 0.04) [15]. In the second trial, mirtazapine also reduced depressive symptoms and improved sleep [15]. A meta-analysis of outcomes for these trials showed consistent signal for

mirtazapine for reduction methamphetamine use, though not for reducing depressive symptoms [16]. The consistent signal across these trials for reducing methamphetamine indicates a need for a phase 3 trial to demonstrate the benefits of mirtazapine when used in a broader population in routine clinical practice.

## 2.2 Objective

The objective of this trial (the Tina Trial) is to establish the effectiveness and safety of mirtazapine as an outpatient pharmacotherapy for methamphetamine use disorder in routine clinical practice in an Australian setting.

## 2.3 Statistical Hypotheses

The primary hypothesis is that oral mirtazapine (30 mg/day for 12 weeks) will, compared to placebo, reduce self-reported days of methamphetamine use.

The secondary hypotheses are that oral mirtazapine (30 mg/day for 12 weeks) will, compared to placebo:

- increase abstinence from methamphetamine use, as assessed by methamphetamine negative oral fluid samples,
- reduce depressive symptoms,
- improve sleep quality,
- reduce HIV risk behaviour, and
- improve quality of life.

# 3 Study methods

## 3.1 Trial design

The Tina Trial is a multi-site double-blind randomised placebo-controlled parallel group, two arm, superiority trial with a 1:1 allocation ratio.

## 3.2 Randomisation

Eligible participants are randomly assigned (1:1) to receive either placebo or mirtazapine based on a computer-generated permuted block randomisation sequence with variable block sizes, stratified by site, sex (male vs. female or other) and depression (PHQ-9 score < 10 vs. 10 or greater) assessed at eligibility.

## 3.3 Sample size

The estimated sample size required for the study (N = 340; 170 per group) was to enable us to detect a minimum rate ratio of 0.75 on our primary outcome (equivalent to a relative reduction from 25 days methamphetamine use in the past 4 weeks at baseline to 20 days use in the past 4 weeks at week 12) with 90% power (two-tailed test,  $p = 0.05$ ). This sample size calculation was based on the effect size found in the most recent trial of mirtazapine for methamphetamine dependence [15] and allows for up to 25% attrition (ie., a final sample of at least 255, or 128 per group, at week 12).

We randomised 344 participants in the trial, of whom 339 participants received the trial medication and 293 completed their week 12 assessment, meeting the sample size requirements estimated above.

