## 6.2 Planned analysis of primary outcome

The analysis of the primary outcome will be based on the intention-to-treat dataset and based on unimputed data. All tests will be two-sided with  $p < 0.05$ .

Descriptive data on days of methamphetamine use will include the median number of days at each time point (baseline, week 4, week 8, week 12 and week 20), with interquartile ranges reported. Variance estimates (i.e., standard errors and confidence limits) will be bootstrapped.

The main effect of medication on days of methamphetamine use will be tested using a mixed model with a group (placebo [0] vs. mirtazapine [1]) by time (baseline [0], week 4 [1], week 8 [2], week 12 [3]) interaction effect, with time entered as a factor variable, producing individual effect estimates for each time point and making no assumptions about the linearity of changes over time. The primary timepoint is week 12. A negative binomial generalised linear mixed model will be used to test this effect. As noted under the general principles above, a random intercept term will be included in the model to account for clustering on repeats [31], and a random intercept term will be included in the model to account for site only if this significantly improves model fit (based on a likelihood ratio test;  $p < 0.05$ ).

Days of methamphetamine use in this model will be based on the past 28 days prior to baseline, and since the previous assessment at the week 4, 8 and 12 assessments (up to 35 days prior to the assessment). Days when the participant was incarcerated or hospitalised will be censored, as per the TLFB guidelines. An exposure term (i.e. offset) will be included in the model to adjust for the exact number of days in each of these periods, because this can vary depending on the actual assessment dates and censoring.

*Interpretation of the treatment effect from the model (i.e., interaction effect rate ratio):* The main treatment effect will be the time (baseline vs. active medication phase) x condition (active vs. placebo) interaction effect, with the primary timepoint being week 12. This interaction effect represents the rate ratio of change in days of methamphetamine from baseline to follow-up (i.e., rate of days of use at baseline/rate of days of use at follow-up) for the active condition, over the rate ratio of change from baseline to follow-up for the placebo condition. That is:

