$$r = (\text{days of use at follow-up} / \text{days of exposure at follow-up}) / (\text{days of use at baseline} / \text{days of exposure at baseline})$$

$r_p = r$  in placebo group

$r_a = r$  in active group

The interaction coefficient representing the treatment effect is the rate ratio (rr) of these two parameters, i.e.,  $r_a/r_p$ .

Thus, the interaction term can be interpreted as the relative difference in the rate of *change* between the intervention and control groups, which allows for random misbalance at baseline rather than assuming baseline methamphetamine use is the same in both groups.

*Analysis of the primary outcome at week 20:* A separate analysis will be conducted to compare days of methamphetamine use in the past 4 weeks at the week 20 assessment. We have chosen to analyse the week 20 endpoint separately because we believe that (a) differences in the conduct of the week 20 assessment may impact data variability (e.g., phone interviews and greater attrition), and (b) there are differences in the clinical interpretation of the outcome at the week 20 assessment (because

participants are no longer on the trial intervention and are offered off-label mirtazapine and other substance use treatment prior to week 20). We will test the main effect of the trial medication on days of methamphetamine use at week 20 using a mixed model with a group (placebo [0] vs. mirtazapine [1]) by time (baseline [0], week 20 [1]) interaction effect. A negative binomial generalised linear mixed model will be used to test this effect. An exposure term (i.e. offset) will be included in the model to adjust for the exact number of days in each of these periods if the observed number of days in the TLFB varies from 28 days. As noted under the general principles, a random intercept term will be included in the model to account for clustering on repeats [31], and a random intercept term will be included in the model to account for site only if this significantly improves model fit (based on a likelihood ratio test;  $p < 0.05$ ).

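### Section 3.3 gives two incompatible targets, a rate ratio of 0.75 and a fall from 25 to 20 days (0.80), and does not show which one the 90% power refers to

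*Combined protocol and SAP*

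**What the plan says.** Section 3.3 sets the sample at "N = 340; 170 per group" in order to "detect a minimum rate ratio of 0.75 on our primary outcome", "with 90% power (two-tailed test", 5% level). In parentheses it describes that ratio as "equivalent to a relative reduction from 25 days methamphetamine use in the past 4 weeks at baseline to 20 days use", with the 20 days falling at week 12. It adds that the sample "allows for up to 25% attrition (ie., a final sample of at least 255, or 128 per group, at week 12", attributes the effect size to the most recent mirtazapine trial, and concludes that the 293 participants assessed at week 12 satisfy the requirement.

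Section 6.2 defines the effect that will be tested. For each arm, r is the follow-up rate of use divided by the baseline rate, and "The interaction coefficient representing the treatment effect is the rate ratio (rr) of these two parameters", active over placebo. The sentence leading into that formula describes each arm's change the other way up, as "rate of days of use at baseline/rate of days of use at follow-up".

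Section 2.1 reports one numerical effect for the most recent trial: "positive urine test results at 24 weeks relative to placebo 63% vs. 74%; RR 0.75".

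**The concern.** A rate ratio and its translation into days should be the same quantity, and here they are not. The days statement is the one clinicians will remember. If the result is null or borderline, readers will ask whether the trial could have detected a drop from 25 to 20 days, and section 3.3 tells them it had 90% power to do so. That may not be true.

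There is also a difference in kind. The days example follows one group from baseline to week 12. The analysis compares two such changes. Without an assumed placebo change, the example does not determine the treatment effect. For instance, if both arms fell from 25 to 20 days, the ratio would be 1.0.

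**Working it through.** **Inputs.** From section 3.3: ratio 0.75; 25 and 20 days; 90% power; two-sided 5% level; 340 randomised; 25% attrition; 255 (128 per arm) at week 12; 293 assessed at week 12. From section 6.2: effect = (active follow-up/baseline) ÷ (placebo follow-up/baseline). No section gives a planning dispersion, standard deviation or within-person correlation.

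**1. The plan's own figures.** Attrition reproduces: 340 × 0.75 = 255, or 127.5 per arm. The 90% cannot be derived forward, because the variance inputs are missing. It can therefore be neither confirmed nor refuted.

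**2. The two targets.**
- 20/25 = 0.80
- 0.75 × 25 = 18.75 days
- Rounding to whole days does not close the gap: the lowest ratio compatible with it is 19.5/25.5 = 0.765.
- On the section 6.2 definition, an active-arm fall from 25 to 20 gives 0.75 only if placebo use rises by a factor of 0.80/0.75 = 1.067, from 25 to 26.7 days. No such rise is stated.

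**3. If the calculation was run at 0.75.** Take the 90% as given and solve for the standard error of the log rate ratio:
- SE = |ln 0.75| / (1.960 + 1.2816) = 0.2877 / 3.2415 = 0.0887

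With no change on placebo, 25 to 20 days is a ratio of 0.80:
- Power = Φ(0.2231/0.0887 − 1.960) = Φ(0.554) = 71.0%

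Two other scales, each set to give 90% at 0.75:
- Negative binomial, n = (z_α + z_β)²(1/μ₁ + 1/μ₂ + 2k)/(ln RR)², with k solved as about 0.46: 71.2%
- Difference in days, 5 against 6.25: Φ(3.2415 × 5/6.25 − 1.960) = Φ(0.633) = 73.7%

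With 293 at week 12 (146.5 per arm), SE = 0.0887 × √(127.5/146.5) = 0.0828:

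| Completers | Power at 0.75 | Power at 0.80 |
|---|---|---|
| 255 (planned) | 90% | 71–74% |
| 293 (achieved, log scale) | about 93% | about 77% |

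For 90% power at 0.80, the requirement is 127.5 × (ln 0.75/ln 0.80)² = 127.5 × 1.66, or about 212 completers per arm (424 in all).

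**4. If the calculation was run on 25 to 20 days.** Power at 0.80 is then the stated 90%, and 0.75 is the mislabelled figure. Power at 0.75 would be Φ(3.2415 × 0.2877/0.2231 − 1.960) = Φ(2.22), about 99%.

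**The case against.** The strongest reply is that the 90% is attached to 0.75, the days are only a parenthetical illustration, and the illustration is simply off. On that view the declared target keeps its power, and with 293 completers it is exceeded. This is a fair reading and may be the right one. It still leaves a false equivalence in the text, and it is the reading under which power for 20 days falls below 90%.

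It can also be said that recruitment is complete, that no model, dataset or significance level changes, and that a null result should be read mainly from its 95% confidence interval. All of this stands, and it makes the point a reporting correction.

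Four stronger readings are tempting, and the documents do not support them.

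- *The trial has only 71% power.* That figure depends on the calculation having been run at 0.75, on no placebo change, and on 255 completers. The plan does not establish the first two, and the trial exceeded the third.
- *The 0.75 is a urine-test relative risk misapplied to days of use.* The match with section 2.1 makes this likely, but no section says so. The crude 63/74 = 0.85 adds nothing, because a reported relative risk may come from a model.
- *The falling blinded medians (24 to 17 days, section 4.7) contradict the planning assumption.* They pool both arms and were observed later. They show neither the placebo arm alone nor what was assumed at planning.
- *The inverted wording in section 6.2 could reverse the result.* Read literally, it would make 0.75 favour placebo. However, the explicit formula that follows, and the coding of placebo and baseline as 0, fix the direction. No analysis changes.

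**Conclusion.** The inconsistency is certain: section 3.3 equates 0.75 with a change that is 0.80, and illustrates a two-arm effect with a one-arm change. Its consequence for power is conditional. On the text's own statement that the target was 0.75, with no placebo change and the standard error implied by 90% power, power for 25 to 20 days is about 71–74% at the planned 255 completers and about 77% at 293. In that case the claim that 293 completers meet the requirement holds for 0.75 (about 93% power) but not for the 20-day target. If the calculation was instead run on 25 to 20 days, the 90% stands for 0.80 and the ratio needs correcting. Either way one published target is wrong. This should be fixed, but the validity and type I error of the primary test are unaffected.

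**What to change.** In section 3.3:
- State which target the calculation used, and correct the other figure. 0.75 corresponds to 25 to 18.75 days, and 25 to 20 days corresponds to 0.80, each against an unchanged placebo arm.
- State the assumed placebo change, the dispersion and the within-person correlation.
- Report power at both 0.75 and 0.80, for the planned and achieved week 12 numbers.
- Limit the statement that the achieved sample meets the requirement to the target actually used.

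The 71–77% figures should not be printed until the sponsor has confirmed from the original calculation that it was run at 0.75. The sponsor should also confirm whether 0.75 came from the urine-positivity relative risk in section 2.1 and, if so, say that it was carried over to a different outcome.

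As a minor correction in section 6.2, change the prose to follow-up over baseline so that it matches the formula.

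The cost is a few sentences and retrieval of the original calculation. No participants are added and no analysis changes. It is best done before unblinding, so that the power statement cannot appear fitted to the result.

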### **3.4 Framework**

Superiority of active medication (mirtazapine) over placebo.

### **3.5 Statistical interim analysis and stopping guidance**

No interim analysis or stopping guidelines were included in the protocol.

### **3.6 Timing of final analysis**

Final analysis will take place after locking the electronic Case Report Form (eCRF) database, which includes all outcome assessments and safety (adverse event) data. This will take place after the final week 20 assessment has been conducted or after the last assessment date that this could have taken place (May 15, 2025).

Analysis of primary and secondary endpoints to be analysed collectively. Sensitivity analyses, subgroup analyses, analysis of tertiary endpoints, and any additional/exploratory analyses, to take place thereafter.

### **3.7 Time points at which outcomes were measured**

The time points at which each of the outcomes were assessed and the measurement timeframe for each outcome assessment is shown in Table 1.

### **3.8 Description of measures**

A detailed description of measures taken in the study is provided in the Appendix. The specific outcomes used in the analysis are detailed in Section 6.

|                                                      | Pre-intervention                    |                     | Intervention (30 mg/day) |                      |                            |                            |                            | Taper dose           | Final medical | Post-study assessment |
|------------------------------------------------------|-------------------------------------|---------------------|--------------------------|----------------------|----------------------------|----------------------------|----------------------------|----------------------|---------------|-----------------------|
| Assessment                                           | Eligibility assessment a | Eligibility medical | Wk 0 (Baseline)          | Wk 2                 | Wk 4                       | Wk 8                       | Wk 12                      | Wk 16                | Wk 18         | Wk 20                 |
| Demographics and drug use history                    | Current/
Lifetime                |                     |                          |                      |                            |                            |                            |                      |               |                       |
| Methamphetamine use disorder (CIDI)                  | Past year                           |                     |                          |                      |                            |                            |                            |                      |               |                       |
| Abstinence from methamphetamine (oral fluid samples) |                                     |                     |                          |                      | Current                    | Current                    | Current                    |                      |               |                       |
| Days of methamphetamine use (TLFB)                   | Past 4 wks                          |                     | Past 4 weeks             |                      | Since last Ax b | Since last Ax b | Since last Ax b |                      |               | Past 4 weeks          |
| Days of other substance use                          | Past 4 wks                          |                     | Past 4 wks               |                      | Past 4 wks                 | Past 4 weeks               | Past 4 weeks               |                      |               | Past 4 weeks          |
| Depression (PHQ-9)                                   | Past 2 wks                          |                     | Past 2 wks               |                      | Past 2 wks                 | Past 2 wks                 | Past 2 wks                 |                      |               | Past 2 wks            |
| Suicidality screener (CSSRS-S)                       | Past month c             |                     | Since last Ax            |                      | Since last Ax              | Since last Ax              | Since last Ax              |                      |               | Since last Ax         |
| Anxiety (GAD – 7)                                    |                                     |                     | Past 2 wks               |                      | Past 2 wks                 | Past 2 wks                 | Past 2 wks                 |                      |               |                       |
| Sleep (AIS-5)                                        |                                     |                     | Past month               |                      | Past month                 | Past month                 | Past month                 |                      |               |                       |
| HIV Risk (HRBS)                                      |                                     |                     | Past month               |                      | Past month                 | Past month                 | Past month                 |                      |               |                       |
| Quality of life (EQ-5D)                              |                                     |                     | Today                    |                      | Today                      | Today                      | Today                      |                      |               |                       |
| Work productivity (WPA-GH)                           |                                     |                     | Past wk                  |                      |                            |                            | Past wk                    |                      |               |                       |
| Patient centred assessment (PGI)                     |                                     |                     |                          |                      | Since Wk 0                 | Since Wk 0                 | Since Wk 0                 |                      |               |                       |
| Tolerability/satisfaction (TSQM II)                  |                                     |                     |                          |                      |                            |                            | Past 2-3 wks               |                      |               | Since last used       |
| Other questions on medication tolerability           |                                     |                     |                          | Current d | Current e       | Current e       | Current                    | Current d |               |                       |
| Health service use                                   |                                     |                     | Past 3 months            |                      |                            |                            | Since Wk 0                 |                      |               | Since last Ax         |
| Body Mass Index – self-report                        | Current                             |                     |                          |                      |                            |                            | Current                    |                      |               |                       |
| Body Mass Index – verified                           |                                     | Current             |                          |                      |                            |                            |                            |                      | Current       |                       |
| Concomitant medications                              | Past 2 wks                          |                     | Since last Ax            |                      | Since last Ax              | Since last Ax              | Since last Ax              | Since last Ax        |               | Since last Ax         |
| Adverse events                                       |                                     |                     |                          | Since Wk 0           | Since last Ax              | Since last Ax              | Since last Ax              | Since last Ax        | f  | Since last Ax         |
| Medication adherence (MEMS®)                         |                                     |                     |                          |                      | Since Wk 0                 | Since last Ax              | Since last Ax              |                      |               |                       |

Notes. aDone within 28 days of Wk 0 bUp to 35 days prior to assessment cTimeframe could vary dOnly one specific questions about known medication side-effects eUnpublished questions on medication tolerability fAdverse events are reviewed by the Trial Physician and information on adverse events may be updated at this timepoint. Abbreviations: Week (Wk), Assessment (Ax), Timeline Followback (TLFB), Patient Health Questionnaire–9 (PHQ-9), Athens Insomnia Scale (AIS), HIV Risk Behaviour Scale (HRBS), Euroqol 5D (EQ-5D), Columbia Suicide Severity Risk Scale Screener (CSSRSS), Patient Global Impression (PGI), Composite International Diagnostic Interview (CIDI) modified to capture a DSM 5 methamphetamine use disorder, the Generalised Anxiety Disorder 7 item scale (GAD-7), Work Productivity and Activity Impairment Questionnaire – General Health V2 (WPAI-GH) Treatment Satisfaction Questionnaire for Medication Version II (TSQM II).

